###### Monthly follow-up of the child till 1st year of age

3.4.2.2.2

All eligible live-born children will be followed up at their homes/nearest Anganwadi centre. To ensure timely and smooth data collection, follow-up visits will be scheduled in a manner that these visits coincide with routine house-to-house visits carried out by CHWs under different ongoing national programs [such as Home-based newborn care (HBNC) and Home-Based Care for Young Child Programme (HBYC) under NHM and “Poshan Abhiyan” (72), “Dastak Abhiyan” specific to MP (73)]. In each monthly follow-up visit, anthropometry, achievement of developmental milestones, and acute morbidity profile will be recorded. Additional information about at-birth APGAR score, weight, length, head, and mid-arm circumference will be collected in the 5th visit (child age 1 month). Blood samples for heavy metal analysis and the data on child immunization and feeding practices will be collected in the 17th visit (during the 12th month of the child’s age).

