###### Study outcomes

3.4.2.3.2

The primary study outcomes are related to childhood growth and development, as shown in Tables 1, 2. In addition, we will also estimate the incidence rate of ARIs (number of episodes of ARI during infancy/total number of children under follow-up). We modified the Integrated Management of Childhood Illness definition for ARI [given by WHO/UNICEF (74)] which has been used previously (75) to create an operational definition of ARI for this study. Modification was done by incorporating the signs and symptoms mentioned in the Integrated Management of Neonatal and Childhood Illness (IMNCI), Ministry of Health & Family Welfare, Government of India. Accordingly, ARI will be defined as cough or difficulty in breathing with or without any general danger signs, with or without any chest indrawing, stridor, and fast breathing. Depending upon the site of inflammation determined by the paediatrician based on clinical signs and symptoms, it will be classified as ARI of the upper respiratory tract and ARI of the lower respiratory tract. Further, depending upon the severity, ARI will be classified as per IMNCI guidelines into “No Pneumonia: cough or cold,” “Pneumonia,” and “Severe Pneumonia or Very Severe Disease.” Based on previous research, we will define each episode of ARI to last for two weeks (75). When a child who has had no symptoms for at least one week develops signs and symptoms of ARI, we will treat that as a new episode (75).

**Table 1 tab1:** Operational definitions, indicators, and measurement methods to be used for child growth-related outcome measures.

Outcome	Operational definition	Variable/indicator	Measurement method
Small for gestational age (SGA)	As per the WHO definition of SGA given by the 1995 WHO expert committee, infants having a birth weight for gestational age below the 10th percentile based on a sex-specific reference population (139, 140).	Proportion of children diagnosed as SGA at birth (proxy of in-utero growth of the child)	Based on hospital records-verified by study staff
Low birth weight (LBW)	Infants with a birth weight of less than 2,500 g, regardless of gestational age at the time of birth (141, 142).	The proportion of children diagnosed as LBW at birth (proxy of in-utero growth of the child)	Based on hospital records-verified by study staff

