Finally, multivariable logistic regression model analyses will be used to study the relationship between environmental variables- PM_2.5_ /PM_10_/blood heavy metal levels and the health outcomes in binary forms – growth/development/ARI. Briefly, multiple linear mixed-effects regression model analyses will be used to study the relationship between the levels of early-life exposure (concentration of environmental pollutants- PM_2.5_ /PM_10_ concentration/ heavy metals in pregnant women and the child participant- monthly means for the former and cumulative mean- i.e., in-utero maternal exposure summed with infancy period exposure to heavy metal) and child health outcomes- mean anthropometric data (height, weight, head, and mid-arm circumference) and developmental level (obtained from developmental quotient/mean score on ASQ-3 scale) of each participant (live-born children) while adjusting for confounders. Similar regression equations will be used to analyze the association between exposure and delay in achieving growth and developmental milestones. Subsequently, the PM_2.5_, PM_10_ data and other environmental/sociodemographic data will be used in a logistic regression model of ARI symptoms within a distributed lag nonlinear modeling framework (DLNM) (88, 89). This approach will test the associations of PM_2.5_ /PM_10_ exposure over the preceding time periods and the distribution of growth z-scores / occurrences of ARI events (90–92).

Analyses will be performed separately for each child’s morbidity outcomes, such as growth/developmental parameters/domain. All analyses will adjust for different confounding variables included in the study. Details of such confounders for statistical adjustment will consist of gender, family size, socioeconomic status, gynecological/obstetrics/other relevant medical history, and data from environmental assessments of the households (built environmental attributes). We will also adjust for the effect of low birth weight and small-for-gestational-age on the studied association (Supplementary material). We will also conduct sensitivity analyses to test the robustness of our findings, for example, analysing a subset with complete data and comparing the results with the entire dataset where missing data imputations have been done.

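### The only model named for the distributed-lag analysis is a plain logistic model of ARI; it is then extended to continuous growth z-scores, and no within-child term is stated for recurrent monthly ARI

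*Protocol article*

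**What the plan says.** Section 3.6 (Statistical analysis and reporting) of the protocol article sets out three regression steps in one paragraph.

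- Multivariable logistic regression for "the health outcomes in binary forms – growth/development/ARI".
- For mean anthropometry (height, weight, head and mid-arm circumference) and developmental level, "multiple linear mixed-effects regression model analyses will be used to study the relationship" with early-life exposure.
- A lag analysis, in which PM and other environmental and sociodemographic data "will be used in a logistic regression model of ARI symptoms within a distributed lag nonlinear modeling framework (DLNM". The next sentence says that this approach will test PM exposure "over the preceding time periods and the distribution of growth z-scores / occurrences of ARI events".

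Two other sections fix the data structure. Section 3.4.2.2.2 states: "In each monthly follow-up visit, anthropometry, achievement of developmental milestones, and acute morbidity profile will be recorded". Section 3.4.2.3.2 makes ARI recurrent: when a child free of symptoms for at least a week "develops signs and symptoms of ARI, we will treat that as a new episode". The ARI measure is "number of episodes of ARI during infancy/total number of children under follow-up", a ratio that can exceed one.

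**The concern.** Two things in the lag analysis do not fit together.

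**Outcome and link.** The distribution of a growth z-score is continuous, and a logistic model needs a categorical outcome. An analyst who follows the sentence literally must either cut the z-scores at a threshold or depart from the text. Growth is among the primary outcomes, so this is not peripheral.

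**Repeated records.** A lag model of ARI occurrence needs events placed in time, so several records per child are the natural layout. Records of one child are correlated. A plain logistic model fitted to pooled child-months takes them as independent and reports standard errors that are too small. Exposure effects would then reach significance more often than the nominal rate.

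**Working it through.** The article states no figure on this point to reproduce. The check is a reading of Section 3.6, then a calculation of what pooling would cost.

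**1. Which model covers the z-scores?** In Section 3.6, z-scores are named for correlation coefficients and again in the lag sentence. The linear mixed models list measured anthropometry and developmental level, not z-scores. The other logistic models are confined to binary outcomes. So there are two readings of the lag sentence:

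- The approach means the logistic lag model: the link does not fit the outcome.
- The approach means the lag framework alone: the link can fit, but no outcome model is named.

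The sentence needs correcting under either.

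**2. Size of the clustering effect if child-months are pooled.**

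Inputs from the article: 571 children (Section 3.3.1) and monthly visits to 12 months (Section 3.4.2.2.2), so T = 12.

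Assumed inputs, not in the article: child-intercept SD of 0.5, 1.0 or 1.5 on the logit scale; share of exposure variance between children (exposure ICC) of 0.2, 0.5 or 0.9; baseline logit −1.7, that is 1/(1 + e^1.7) = 15% per month for an average child; true exposure effect zero.

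Approximate variance inflation:

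DE = 1 + (T − 1) × ICC_outcome × ICC_exposure

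Example: 1 + 11 × 0.131 × 0.9 = 2.30. The true standard error is then √2.30 = 1.52 times the reported one. The expected rejection rate is 2 × [1 − Φ(1.96/1.52)] ≈ 0.20, close to the simulated 17.8%.

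Simulation with ordinary logistic regression, 600 runs per setting, nominal 5%:

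| Child SD | Outcome ICC | Exposure ICC | DE | Type I error, independence | Type I error, child-clustered |
|---|---|---|---|---|---|
| 0.5 | 0.03 | 0.2 | 1.07 | 6.5% | 5.7% |
| 0.5 | 0.03 | 0.5 | 1.18 | 6.2% | 5.2% |
| 0.5 | 0.03 | 0.9 | 1.33 | 9.7% | 5.5% |
| 1.0 | 0.13 | 0.2 | 1.29 | 9.7% | 5.5% |
| 1.0 | 0.13 | 0.5 | 1.72 | 13.0% | 4.2% |
| 1.0 | 0.13 | 0.9 | 2.30 | 17.8% | 4.5% |
| 1.5 | 0.25 | 0.2 | 1.56 | 9.7% | 5.2% |
| 1.5 | 0.25 | 0.5 | 2.39 | 16.5% | 4.5% |
| 1.5 | 0.25 | 0.9 | 3.51 | 33.0% | 7.3% |

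The Monte Carlo standard error at 5% is √(0.05 × 0.95/600) = 0.9 percentage points, so the two lowest entries (6.2% and 6.5%) are barely distinguishable from 5%. The number of children does not enter DE.

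**3. Size of the loss if z-scores were cut.** The information kept by dichotomising a normal variable is φ(z)²/[p(1 − p)]:

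- p = 0.084: z = −1.379, φ = 0.154, giving 0.0238/0.0769 = 0.31.
- p = 0.212: z = −0.800, φ = 0.290, giving 0.0840/0.1671 = 0.50.

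The article gives no baseline stunting proportion. These two values are assumptions, chosen because they are roughly compatible with 571 and the odds ratio of 1.74, read as a per-group size or as a total.

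**The case against.** The logistic model is attached by name to ARI symptoms only. The reference back to the approach, followed by preceding time periods, can fairly be read as the lag framework, which works with an identity link as well as a logit. The authors separate binary from continuous outcomes in the same paragraph. This is a fair reading. It turns the mismatch into loose wording, but still leaves the lagged z-score analysis without a named model.

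A reader might infer that the z-scores will be dichotomised and half or more of their information lost. The documents do not support that: no section says that they will be cut for the lag analysis, so the 31% to 50% is conditional.

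A reader might also infer that the plan ignores repeated records of the same child. That too goes beyond the text. The unit of analysis and the variance estimator for the ARI lag model are not stated, and a condensed article may leave them to the full protocol or analysis plan. What stands is the contrast within one paragraph: mixed effects are written in for the linear models and absent from the logistic lag model, whose outcome is recorded monthly and recurs. One record per child would avoid the correlation but discard the recurrent episodes that Section 3.4.2.3.2 defines.

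The simulation has no lag basis, and its upper end needs both strong child-level heterogeneity and exposure that varies mostly between children. Assigning ambient PM by home geocode makes a sizeable between-child share plausible. But the Discussion concedes that land-use regression separates clustered addresses poorly, and a lag analysis also uses variation over time.

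**Conclusion.** The point holds as a specification fault in the lag analysis, not as proof that a wrong analysis will be run. The z-scores have either an unsuitable model or none. The logistic lag model carries no stated within-child term.

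If child-months are pooled as written, true type I error for an ARI exposure term is about 6% to 33% at nominal 5%, and the variance is understated by a factor of about 1.1 to 3.5. Child-clustered errors bring type I error back to about 4% to 7%. These figures rest on the assumed ICCs and on ordinary logistic regression, so they show direction and rough size for the lag model rather than an exact error rate.

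No design figure changes. It should be put right before analysis, but it does not threaten the study.

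**What to change.** In Section 3.6, split the lag sentence into two:

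- **Growth z-scores:** an identity-link (linear mixed) distributed-lag model on the repeated monthly z-scores, with a child random intercept.
- **ARI:** a logistic or count distributed-lag model, with a child random intercept or child-clustered robust standard errors. State the unit of analysis (for example child-month).

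The cost is a change of wording, standard mixed-model code and slightly wider ARI intervals. No extra data or participants are needed.

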### Ethical considerations

3.7

This study was reviewed and approved by the Institutional Ethics Committee (Human), National Institute for Research in Environmental Health (vide approval letter number: ICMR-NIREH/BPL/IEC/2023–24/1307 dated 16/02/2024). At the beginning of the research, we will obtain written informed consent from the pregnant women for both their and their child’s participation, allowing data collection and scientific dissemination. If we identify any pregnant women or children with signs of illness or health complications during our survey, we will refer them to a nearby government hospital. We will inform the study participants and their families about the study’s final findings through meetings organized in the community with the help of the CHWs. We will also disseminate the findings scientifically through the publication of peer-reviewed articles.

## Discussion

4

The ELitE birth cohort study will be a relevant addition to the currently sparse evidence base about the long-term effects of early-life exposure to air pollutants among Indian children. Owing to physiological pulmonary adaptation during pregnancy, women inhale a higher volume of air and the pollutants in it in each respiratory cycle (93). Adverse health effects in the mother coupled with the now-acknowledged potential of PM to cross the placenta cause placental malfunctioning as well as other direct and indirect environmental insults to the susceptible developing fetus (94–98). Postnatally, multiple factors such as higher baseline ventilation rates, predominance of mouth-breathing bypassing nasal clearance of particles, and immature immune/pulmonary systems contribute to both higher risk of PM exposure and increased inhaled doses post similar levels of exposure in children who have different deposition and clearance probabilities than adults (99). Hence, pregnant women and children, particularly those living in low-resource, high-exposure settings like India, are especially vulnerable to the adverse health effects of air pollution. Therefore, it is essential to collect prospective longitudinal data to document and understand these impacts over time.

The adverse effects of PM exposure on child growth/developmental trajectory have been shown by epidemiological studies, albeit with contradictory findings (13–17). However, the biological mechanisms mediating these effects are not well explored, leading to perpetuating ambiguity (100). Recently, Sinharoy et al. (101) attempted to elucidate the pathophysiological framework underlying the exposure-response relationship between air pollution and stunting. Authors posited that antenatal exposure via oxidative stress and inflammation leads to mitochondrial dysfunction, decreased DNA methylation, and shortened telomere length, all of which contribute to placental dysfunction and poor foetal growth (101). Further, authors argue that adverse effects on developing immune and pulmonary systems affecting the child’s susceptibility to infections compounded by alterations in appetite versus bodily requirements and dietary metabolite absorptions vis-à-vis loss, particularly that of vitamin D, can contribute to post-natal growth failure leading to stunting (101). Other researchers have also reported similar mechanisms (102, 103). Growth failures due to chronic malnutrition during early childhood can independently translate into developmental delay (104, 105).

On the other end of this spectrum, research has found links between PM exposure and adiposity. The association between PM and obesity is well-established among older children and adults, as shown by a recent review (106). It is said to be mediated via many mechanisms ranging from oxidative stress/inflammation and epigenetic changes to perturbations in metabolic and intestinal flora balance (106). However, the common postulation explaining this dichotomy in the PM effect on growth trajectory reasoned that children with early-life growth restriction are at higher risk of metabolic diseases, including obesity, at a later phase in life as per the developmental origins of health and disease (107, 108). However, recent evidence challenges this mode of reasoning since obesity and higher adiposity have been noted among exposed infants (18, 19). Another line of thinking has evolved, which contemplates that the phenotype of fetal growth restriction in an antenatally exposed mother could be immediately followed by rapid weight gain in the infancy period (109). However, the overall paucity of longitudinal evidence precludes the drawing of any conclusions. The study presented here will help fill in the existing gap in knowledge owing to the scarcity of longitudinal evidence by establishing a birth cohort consisting of mother–child pairs from two urban areas of central India. Although findings are not expected to be generalizable globally, the prospective follow-up data collected in this cohort study will provide strong evidence for planning and policymaking in this field.

This study has multiple advantages owing to its multi-disciplinary research team, which aids in comprehensive information collection and enhances the validity of the study’s findings. Such a strength would be crucial since we deal with child growth and development, a complex multidimensional concept (110, 111). Children are vulnerable to the effects of the complex interplay between a multitude of factors ranging from environmental and psychosocial to genomic insults (112). These factors are hypothesized to begin their effect even before conception (113). Therefore, researchers are increasingly acknowledging the concept of the “exposome,” first introduced in 2005, as the entirety of all non-genomic influences from conception to death owing to the internal effects from the human bodily environment and external influences encompassing harmful exposures to chemical pollutants/infectious pathogens, health behavioral factors linked to tobacco/alcohol consumption, physical activity or diet and even societal, economic, psychological and spiritual factors (114, 115). However, accounting for all potential exposure and confounder variables is a humongous task demanding high-end infrastructure, cost-intensive analytic methods, and high-dimensional data computational facility, all limited in low-resource settings (116). Therefore, although we have not been able to incorporate multiple exposures such as residential greenness, high-decibel community noise, water/food pollutants such as pesticides, endocrine disrupting chemicals, etc., with known effects on child growth/developmental trajectory and morbidity profile (117–123), and “omic” technologies; we have planned for this longitudinal transgenerational study with follow-up at regular intervals and biological sampling to initiate the investigation in this field in India. As evidence from similar cohorts begins to accumulate, the opportunity for robust data analysis will expand. In the future, the evidence base can be strengthened by merging collected exposure and health outcome data with advanced analyses of stored biological samples, similar to the approach used by the EXPOsOMICS research group (124).

A limitation of this exposure-response cohort is the potential of missing personal exposure information in the first trimester. Considering operational feasibility, the 16^th^ week was chosen as the cut-off for pregnant women’s enrolment and the start of exposure assessment in the antenatal period. Previous research has shown that most women in India report their first antenatal care visit within a median time of 16 weeks of gestation, and only 19.6% of pregnancies are detected and registered within the first trimester (125, 126). Hence, it is likely that we will be enrolling most of our pregnant participants in the gestational period of the 12th -16th week, and our field-data-based exposure assessment will fail to account for the complete picture of first-trimester exposure. This can be a significant limitation since it is plausible that the sensitive window for exposure in this context can be during the first trimester. Data analyzed from the INMA Spanish birth cohort showed that the z-score for length at the 6th month of the child’s age reduced by 6% for every 10-μg/m^3^ increase in antenatal NO_2_ exposure during the first trimester (127). Block and Calderón-Garcidueñas (128) also stated that first-trimester exposure to organic constituents of PM, such as polycyclic aromatic hydrocarbons, had a maximal effect on fetal growth when compared with later exposures. This limitation affects birth cohorts in low- and middle-income countries in Asia and Africa. For example, a rural Ghanaian pregnancy cohort investigating air pollution and childhood growth trajectory enrolled pregnant women at or before the 24^th^ week of gestation (15). Authors would have been facing similar constraints as us since the median time to first visit for antenatal care among African women has been reported to be 5 months (129).

We have attempted to overcome this limitation by incorporating past exposure open-access data (such as CPCB ground monitoring stations/satellite-based estimates) of PM_2.5_ into our constructed LUR models. Previous studies have used this method. For example, the recently published Californian population-based prospective pregnancy cohort study (MADRES) enrolled pregnant women with a gestational age of less than 30 weeks and obtained air pollution exposure information using data from the United States Environmental Protection Agency Air Quality System to model daily participant exposure beginning from 2 years before pregnancy (130). However, using only LUR modeling-based exposure assessment suffers from ecological fallacy (131). Final estimation is highly dependent upon the density of monitoring stations from which PM data can be used to train the models and the granularity of data for predictor variables and, thus, cannot accurately differentiate between individual-specific exposure, particularly when their residential addresses are clustered close together (132, 133). Hence, data triangulation by adding personally measured and biomonitoring data would increase confidence in the overall exposure assessment (134). We have thus adopted a multi-pronged strategy to estimate the study participants’ accurate exposure information.

Finally, to ensure the highest level of internal validity of our study, we will attempt to overcome the biases inherent in adopting a cohort study design (135, 136). For example, to control for attrition bias, loss-to-follow-up will be minimized through better rapport building with the study participants with the support of CHWs. Published evidence acknowledges the crucial role played by CHWs, who are usually residents of the locality where they work and, hence, have an established rapport with their beneficiaries (137, 138). By seeking the active cooperation of CHWs through appropriate incentivization, we will be leveraging this trust built with the community. Hence, we expect attrition to be minimal in the study. In addition, we will also systematically document the characteristics (including the reasons for withdrawal) of those participants who decline further follow-up. Although not wholly amenable to control, other selection biases like non-response bias and healthy entrant bias will be accounted for by asking for and recording relevant information about those pregnant women who refuse to participate in the study when approached for consent (135, 136). Similarly, information and confounding bias will be minimized by ensuring the use of validated pilot-tested questionnaires and appropriate collection of data on exposure, outcome, and confounding variables by trained research staff (135, 136).

